## Methods

### Study design

We will conduct a two-armed randomized controlled trial (RCT). Participants will be randomly assigned to one of two conditions: Family Connections (FC) or Treatment As Usual (TAU). Block randomization will be carried out among the three clinical centers, considering that if a patient has more than one family member who attends the group, they will be randomized together to be included in the same condition. Measures will be taken before starting the intervention, after the intervention, and at the 6-month follow-up to determine whether improvements after the intervention are maintained in the long term. The study flowchart appears in Fig. 1. We will follow the CONSORT statement (Consolidated Standards of Reporting Trials, http://www.consort-statement.org) [31, 32] and the SPIRIT guidelines (Standard Protocol Items: Recommendations for Interventional Trials) [33, 34].

**Fig. 1 Fig1:**
[figure not shown]
Flowchart of the study

### Sample size

To determine the sample size, the effect sizes found in the literature on the subject have been considered. The controlled study by Grenyer et al. [35], which tested a group psychoeducation protocol for caregivers of people with BPD, reported medium to large effect sizes (dyadic adjustment, *d* = .78; family empowerment, *d* = 1.4). In addition, on measures of burden, Grenyer [35] reported significant improvements between post assessment and the 12-month follow-up, with medium effect sizes (Burden Assessment Scale, *d* = .45). These effects are consistent with the literature on psychological treatments for other psychiatric disorders, such as the meta-analysis of psychological interventions for caregivers of people with bipolar disorders (Burden, *g* = −.80) [36].

Taking these data into account, in the present study, adopting a conservative approach, an effect size of 0.60 is expected because our design includes two experimental conditions. Considering an alpha of 0.05 and a statistical power of 0.80 on a 2-tailed *t* test, the total sample size needed to reach an effect size of 0.60 for burden is 90 participants (45 participants per experimental condition). To control the maximum possible loss of participants during treatment, based on the literature about programs for family members of patients with BPD, a 29% dropout rate is expected [20, 23–25, 27]. Thus, the required sample size should be a total of 116 participants (58 participants per group). These calculations were made with the software program G*Power 3.1 [37].

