#### Treatment as usual (TAU)

Treatment as usual is the program routinely offered to BPD patients’ relatives in the clinical centers participating in this trial. The intervention includes 12 therapeutic sessions in six modules. Each module has specific objectives and practical exercises.
*Introduction*. This module consists of an overview of the treatment and the aims of the group. Furthermore, it focuses on the definition of personality disorders, BPD and its clinical characteristics, the role of emotion regulation, and comorbid disorders.*Family Education*. The aim of this module is to explain the diagnostic criteria for BPD, associated problems (alcohol and substance use and eating disorders), the DBT model, and the main goals of the treatment.Validation Skills. The purpose of this module is to explain what validating and invalidating environments are, the consequences of an invalidating environment, and how to use validating skills.*Crisis Management Skills*. This module aims to prevent crises by explaining how to manage anger and learning how to act in the presence of self-injuring and suicidal behaviors. Moreover, acceptance skills are shown in this module.*Problem Management Skills*. This module helps the relative to know how to deal with problems and set clear limits, handle conflict in everyday situations, confront unacceptable behavior, and manage emotionally charged conversations.*Relapse Prevention*. It aims to strengthen the strategies learned throughout the program, schedule future practice, and teach the participants how to identify and cope with future high-risk situations.

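### The planning effect of 0.60 for burden is labelled conservative, but the only effect cited on the BAS is 0.45, and no cited between-arm BAS effect supports 0.60

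*Protocol article*

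**What the plan says.** The Sample size section of the protocol article cites four effects. Three come from a controlled study of group psychoeducation for caregivers of people with BPD: dyadic adjustment (d = 0.78), family empowerment (d = 1.4) and burden. For burden, that study "reported significant improvements between post assessment and the 12-month follow-up", "with medium effect sizes (Burden Assessment Scale, *d* = .45". The fourth is g = −0.80 for burden, from a meta-analysis in caregivers of people with bipolar disorder, with no scale named.

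The plan then chooses its value: "adopting a conservative approach, an effect size of 0.60 is expected because our design includes two experimental conditions". With alpha 0.05 and "a statistical power of 0.80 on a 2-tailed *t* test", it derives 90 participants (45 per arm) for burden. It expects 29% dropout and enrols 116 (58 per arm).

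The BAS is one of two primary outcomes (Abstract; Primary outcomes). The Background calls TAU an active treatment condition, and the TAU section says of it: "The intervention includes 12 therapeutic sessions in six modules". The Data analyses section plans a repeated-measures ANOVA or MANOVA over pretreatment, post-treatment and follow-up, with arm as the between-subject factor.

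**The concern.** A planning effect is conservative if it sits at or below the most relevant evidence. Of the four cited effects, two concern burden, and only one of those is on the scale and in the caregiver population of this trial. That one is 0.45, and 0.60 is a third larger (0.60/0.45 = 1.33). The two effects furthest from the planned outcome, dyadic adjustment and family empowerment, are not burden measures.

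The reason given, that there are two experimental conditions, does not lead to 0.60 in particular. TAU has the same number of sessions and modules as FC, and both have introduction, family education, validation and problem-management modules. Hypothesis (a) expects both arms to improve on burden. All this points towards a modest contrast between arms, and the section does not say why 0.60 is the right size for it.

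At stake is how the result will be read. A reader told that the trial has 80% power under a cautious assumption may give a non-significant burden comparison more weight than the design can bear.

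**Working it through.** **Inputs (all from the Sample size section).** Two-sided alpha 0.05; two-sample t test; 1:1 allocation; d = 0.60 (planned) and d = 0.45 (cited BAS effect); 45 per arm analysed; 58 per arm enrolled; 29% dropout.

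**Formula.** With n per arm, the noncentrality is δ = d·√(n/2) on 2n − 2 degrees of freedom. Power is the probability that a noncentral t variable with this δ falls beyond the two-sided 5% critical value.

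**Step 1: the plan's own figure.** For d = 0.60 and n = 45, δ = 0.60 × √22.5 = 2.85, with critical value 1.987 on 88 df. Power is 0.804. With 44 per arm it is 0.795, so 45 per arm (90 in total) is the smallest size that reaches 0.80. The stated figure is reproduced.

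**Step 2: analysed numbers.** The enrolment of 116 equals 90 × 1.29 = 116.1. With 29% lost, 58 × 0.71 = 41.2, so about 41 per arm (82 in total) remain. If everyone enrolled is analysed, there are 58 per arm.

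**Step 3: power at both values.**

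| Analysed per arm | d = 0.60 | d = 0.45 |
|---|---|---|
| 45 | 0.80 | 0.56 |
| 41 | 0.77 | 0.52 |
| 58 | 0.89 | 0.67 |

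Power of 0.80 at d = 0.45 would need 79 analysed per arm. The fall from 0.80 to 0.77 at d = 0.60 comes from the dropout allowance, not from the choice of effect.

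**Step 4: what a confidence interval can exclude.** In SD units the unadjusted 95% half-width is t × √(2/n). With 45 per arm this is 1.987 × √(2/45) = 0.42; with 41 per arm it is 1.990 × √(2/41) = 0.44.

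**Step 5: use of baseline BAS.** The documents give no baseline-to-post correlation r, so 0.5 to 0.7 is an assumption. A pre-post change contrast, as in the time-by-arm part of the planned repeated-measures analysis, has effective size d/√(2(1 − r)). With baseline as a covariate it is d/√(1 − r²). At r = 0.6, for example, these are 0.45/√0.8 = 0.503 and 0.45/√0.64 = 0.5625. Power at d = 0.45:

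| r (assumed) | Change, 45 per arm | Covariate, 45 per arm | Change, 41 per arm | Covariate, 41 per arm |
|---|---|---|---|---|
| 0.5 | 0.56 | 0.68 | 0.52 | 0.64 |
| 0.6 | 0.66 | 0.75 | 0.61 | 0.71 |
| 0.7 | 0.78 | 0.84 | 0.74 | 0.80 |

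All these figures treat participants as independent, as the plan's own calculation does.

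**The case against.** Four arguments count against the point.

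- **The label has some basis.** The value 0.60 is below three of the four cited effects, including the only pooled burden estimate. The clause about two experimental conditions can be read as the reason for going below those values because TAU is active. How far to go is a planning judgement. This stands, so the label is wrong only in relation to the BAS figure.

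- **The 0.45 is not a like-for-like benchmark.** It is described as a change after treatment ended, not as a difference between arms. A reader might infer that the trial's real power is 0.56, little better than a coin toss. The document does not support that: 0.45 is not shown to be the between-arm effect to plan for, and 0.56 is a sensitivity figure. The same fact leaves 0.60 without a cited between-arm BAS source.

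- **Low power does not settle what a null result excludes.** A reader might infer that a non-significant result could not rule out 0.45 SD, or any effect below about 0.6 SD. That confuses the detectable effect with the confidence interval. With a half-width of about 0.42 SD, an estimate near zero would exclude 0.45. An estimate that favours FC but is not significant could leave 0.45 and more inside the interval.

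- **The planned analysis already uses baseline.** Pretreatment is a level of the within-subject factor, so the gain from a baseline covariate must be measured against a change contrast and not against a post-only t test. This is right, and the last table makes that comparison. At r = 0.5 the change contrast gains nothing over the post-only test.

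**Conclusion.** The point holds in a limited form. The arithmetic behind 45 per arm is correct. What is wrong is the description: 0.60 is not conservative against the one cited effect on the primary burden scale, and none of the cited effects is a between-arm BAS effect that would justify it. At 0.45, none of the three analysed sizes reaches 0.80 with the planned t test; power runs from 0.52 to 0.67. Under the plan's own dropout rate, the power at 0.60 is about 0.77.

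The power figures rest on the two-sided t test that the plan names, equal arms and independent participants. The covariate figures also rest on the assumed correlations. The condensed article format does not explain the issue away, because the choice of effect and its rationale are stated in this section.

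**What to change.** No extra participants are needed.

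1. In the Sample size section, delete or qualify the claim of a conservative approach. Say that 0.60 lies between the two cited burden effects (0.45 and 0.80), and that the 0.45 is not described as a between-arm effect. Report power at both planning values (0.60 and 0.45): 0.80 and 0.56 with 90 analysed, 0.77 and 0.52 with 82 analysed.
2. State that a non-significant burden result will be interpreted from the between-arm estimate and its 95% confidence interval (half-width about 0.42 SD with 45 per arm, unadjusted). Do not add a general sentence that effects below some size cannot be ruled out.
3. Analyse post-treatment BAS by arm with baseline BAS as a covariate. Table 1 shows that baseline BAS is already collected. Under the assumed correlations this is more efficient than the change contrast, by 6 to 12 percentage points of power at d = 0.45 (0.84 against 0.78 at r = 0.7 with 45 per arm; 0.68 against 0.56 at r = 0.5 with 45 per arm).

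The cost is a reworded paragraph, one covariate in the model, and a stated power that looks less favourable.

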**Methods:**

The study is a randomized controlled trial. The participants will be recruited in a Personality Disorders Unit and randomly assigned to one of two treatment conditions: *Family Connections group (FC)* or Treatment As Usual (TAU). Primary outcome measures will be the BAS and FAD-GFS. Secondary outcomes will include DASS-21, FES, GS, and QLI. Participants’ treatment acceptance and degree of satisfaction will also be measured. Participants will be assessed at pre-, post-treatment, and 6-month follow-up. Intention to treat and per protocol analyses will be performed.

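### The 29% dropout allowance was applied as 90 × 1.29 instead of 90 / 0.71, so 116 participants leave about 82 completers, not the 90 needed for 80% power

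*Protocol article*

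**What the plan says.** The whole derivation is in one paragraph of the protocol article, Methods, Sample size.

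- **Test, error rate and power:** "Considering an alpha of 0.05 and a statistical power of 0.80 on a 2-tailed" t test.
- **Effect:** "an effect size of 0.60 is expected because our design includes two experimental conditions". The effect is standardised and refers to burden.
- **Number needed before any allowance for loss:** "the total sample size needed to reach an effect size of 0.60 for burden is 90 participants (45 participants per experimental condition").
- **Expected loss:** "a 29% dropout rate is expected", introduced with the words "To control the maximum possible loss of participants during treatment".
- **Conclusion:** "Thus, the required sample size should be a total of 116 participants (58 participants per group").

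The inflation formula is not given. The abstract adds: "Intention to treat and per protocol analyses will be performed".

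**The concern.** The final total is presented as the direct result of 90 participants and a 29% dropout rate, but the two do not produce 116 when the rate is applied to the people enrolled. Multiplying the required number by one plus the dropout rate is a common slip. It treats dropout as a fraction of the completers, although the people who drop out come from the larger enrolled group.

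What is at stake is the stated power. The section on study population and recruitment says recruitment continues until the required sample is reached, so 116 is the number at which it would stop. If 29% are then lost, the trial is smaller than the size on which its 80% power rests.

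**Working it through.** **Inputs, all from the Sample size section:** two-sided two-sample t test, alpha 0.05, target power 0.80, standardised effect d = 0.60, equal arms, dropout 29%.

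**Step 1: the base figure.** Power from the noncentral t distribution, with n per arm, 2n − 2 degrees of freedom and noncentrality d × √(n/2):

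- The exact solution for 80% power is n = 44.6 per arm.
- n = 44 gives power 0.795; n = 45 gives 0.804.

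So 45 per arm, 90 in total, is reproduced. It is the smallest equal-arm size that reaches 80%, so it has no slack to absorb a shortfall.

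**Step 2: the printed total.**

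- 90 × (1 + 0.29) = 116.1, and 45 × 1.29 = 58.05. Both match the printed 116 and 58.
- 90 / (1 − 0.29) = 90 / 0.71 = 126.8, so 127. With equal arms, 45 / 0.71 = 63.4, so 64 per arm and 128 in total.
- Starting instead from the normal-approximation base of 44 per arm (88 in total), 88 / 0.71 = 123.9, so 124. This is not 116 either.

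Of these, only the multiplication by 1.29 gives the printed figures. The shortfall at enrolment is 127 − 116 = 11, or 128 − 116 = 12 with equal arms.

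**Step 3: what 116 leaves.**

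- Completers at 29% loss: 116 × 0.71 = 82.4, or 58 × 0.71 = 41.2 per arm. That is about 8 fewer than 90.
- Highest dropout that still leaves 90: 1 − 90/116 = 26/116 = 22.4%.

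**Step 4: power for d = 0.60 (same t test).**

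| Situation | n per arm | Power |
|---|---|---|
| As planned, 90 completers | 45 | 0.804 |
| 116 enrolled, 29% lost | 41 | 0.765 |

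With the fractional 41.18 per arm the power is 0.767, so about 0.77 either way. The effect detectable with 80% power at 41 per arm is d = 0.626, about 0.63.

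**Step 5: the corrected total.** 128 × 0.71 = 90.9 completers, which meets the requirement of 90.

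**The case against.** Four points can be made for the plan.

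1. **The effect is small.** Power falls by about four points (0.804 to 0.765). The uncertainty in the assumed effect matters far more. The same section cites d = .45 for the same burden scale and d = .78 for dyadic adjustment. At .45, power is 0.56 with 45 per arm and 0.52 with 41; at .78 it is 0.96 and 0.94. In neither case does the slip decide whether the trial is large enough. This stands as a comment on practical weight. It does not make 116 follow from 90 and 29%.

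2. **The 29% may be a worst case.** It is introduced as a maximum possible loss. With 116 enrolled, power is 0.816 at 20% loss and 0.79 at 25%, and it stays at or above 0.80 up to about 22%. So the shortfall is conditional on the loss that occurs. But the same sentence also calls 29% the expected rate, and an allowance set to cover a maximum should cover it.

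3. **Intention to treat may retain the dropouts.** If all 116 contributed outcomes, t-test power would be 0.89. Yet the paragraph inflates precisely because it treats dropouts as lost; otherwise no allowance would be needed. The article names repeated-measures ANOVA and MANOVA, which in their usual form omit incomplete cases. It states no method for recovering dropouts' information, and its Discussion says people who leave treatment are hard to contact. What stands is that 0.765 is a complete-case figure.

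4. **The t test is not the planned analysis.** The plan uses a repeated-measures model, randomises relatives of one patient together, and treats participants in groups. The t-test figures are therefore not the trial's true power. This limits how far they can be read, but the correction concerns the paragraph's own arithmetic, which uses the t test.

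**Conclusion.** The concern holds. The figure of 116 (58 per group) is an arithmetic error on the document's own inputs; the correct total is 127, or 128 with equal arms. If the full 29% is lost from analysis, about 82 participants remain and power at d = 0.60 is about 0.77, not 0.80.

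This rests on three assumptions, all taken from the paragraph itself: the two-sided t test, the effect of 0.60, and dropouts contributing nothing to the analysis. Below about 22% loss, 116 would be enough. The 29% refers to loss during treatment, so any further loss before the 6-month follow-up would reduce the number below 82. The practical effect is modest, but a figure the trial relies on is wrong as written and should be corrected.

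**What to change.** Correct the last step of the Sample size paragraph in one of two ways.

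- **Keep 116.** State that at 29% dropout about 82 participants remain, giving power of about 0.77 for d = 0.60. Equivalently, state that the detectable effect at 80% power is 0.63, or that 116 allows for 22% dropout.
- **Keep 80% power at 29% dropout.** State the requirement as 128 participants (64 per group), from 90 / 0.71.

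Either way, show the formula so the reader can check it. The first option costs one sentence and a slightly less favourable power statement, with no extra recruitment. The second costs 12 more participants. The Data Availability statement describes the trial as still recruiting, so both appeared open when the article was written.

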### Study population, recruitment, and eligibility criteria

The sample will consist of relatives of people with BPD. Recruitment will be carried out among relatives of patients treated at clinical centers specializing in the treatment of BPD in the Valencian region. Inclusion criteria will include the following: a) being 18 years old or more; b) having a family member diagnosed with BPD; c) ability to understand and read Spanish; and d) providing written informed consent. Participants will be recruited by clinicians working in these clinical centers in three Spanish cities (Castellón, Valencia, and Alicante), until the required sample is complete. Clinicians will offer patients’ families the opportunity to participate in the study and, after explaining it, obtain their informed consent. All the psychologists who participate in this research will have at least a master’s degree in Clinical Psychology and specialized FC training.

A psychologist will contact the participant to determine his/her inclusion in the study. At that time, the researcher will collect the baseline data and determine whether the inclusion criteria are met (see Table 1). Then the psychologist will contact a person outside the research group who will perform the individual randomization and inform the assessor of a code that corresponds to the type of treatment. This psychologist will be unaware of the characteristics of the study.

**Table 1 Tab1:** Study measures and evaluation times

Participant	Measure	Aim	Evaluation time
Caregiver	S-D Interview	Diagnosis	BL
	BAS	Severity of burden symptoms	BL, Post-T and FU
	FAD-GFS	Familiar Global Functioning	BL, Post-T and FU
	DASS-21	Depression, anxiety and stress symptoms	BL, Post-T and FU
	FES	Family empowerment	BL, Post-T and FU
	QLI-Sp	Quality of life	BL, Post-T and FU
	OTSM	Treatment opinion and acceptance	PM
Patient	FAD-GFS	Familiar Global Functioning	BL, Post-T and FU
	DASS-21	Depression, anxiety and stress symptoms	BL, Post-T and FU
	DERS	Difficulties in emotional regulation	BL, Post-T and FU
	LEAP	Emotional availability of parents	BL, Post-T and FU
	VIRS	Validating and invalidating responses	BL, Post-T and FU

*BL* Baseline; *Post-T* Post-treatment; *FU* 6-month follow up; *OTSM* Opinion of Treatment Scale by Modules; *S-D interview* Socio-Demographic Interview; *BAS* Burden Assessment Scale; *FAD-GFS* Family Assessment Device – Global Functioning Scale; *DASS-21* Depression, Anxiety and Stress Scale; *DERS* Difficulties in Emotion Regulation; *FES* Family Empowerment Scale; *QLI-SP* Quality Life Inventory-Spanish version; *GS* Grief Scale; *LEAP* Lum Emotional Availability of Parents; *VIRS* Validating and Invalidating Responses Scale

The psychologist will ensure that the participant has understood the characteristics of the study, and he/she will answer any questions the participant has. Participants will agree (or not) to participate before knowing which intervention condition they will be assigned to. The participants will also be informed that they can leave the study whenever they wish, and that in no case will there be any negative consequences for their family member who is receiving treatment at the center.

The psychologists who will participate in this study have extensive experience in implementing the DBT program for patients and will receive training in the FC program.

### Ethics

The study will follow the Declaration of Helsinki Guidelines and existing guidelines in Spain and the European Union for the protection of participants in clinical trials. The Ethics Committee of the University of Valencia (Valencia, Spain) has approved this study. The trial was registered at clinicalstrial.gov as NCT04160871, registered the 15th of November of 2019.

Sample recruitment will be carried out by qualified clinicians. Researchers will explain the study to the participants, and they will sign the consent form as volunteer participants with the possibility of dropping out at any time. If our hypotheses are confirmed, the FC condition will be offered to participants assigned to the TAU condition after the 6-month follow-up. Special difficulties are not expected, based on the literature. If a participant drops out of the trial due to unwanted events, s/he will have the opportunity to participate the next time the treatment groups for family members are offered.

To protect information, personal data (e.g. age, sex, address, mail, phone) will be collected by the researchers participating in this study, and data will be replaced by codes. Personal data will be strictly separated from other data, and it will only be available to researchers responsible for the study, always considering and protecting the right to privacy of the participants.

